#### Quality of life/care

Affected women’s quality of life as well as experienced quality of care will be measured using a structured survey of all women who gave their consent to participate in this study. For this purpose, we adapted the “diabetes quality of life questionnaire” developed by Burroughs and colleagues [14].

#### Adoption of the intervention at health center level

Perceptions of providers in the intervention facilities regarding the new model of screening and initial management, the feasibility of GDM screening and follow-up at primary level, as well as facilitating factors and challenges for daily practice will be assessed through focus group discussions with providers.

#### Prevalence of GDM

Prevalence of gestational diabetes will be measured at the primary health care level using as numerator the number of women tested positive for GDM and as denominator the number of pregnant women tested.

### Data collection

Data will be collected monthly at health center level. Individual data of patients diagnosed with GDM who consented to participate in the study will be collected by data collectors based at the health facility on a daily basis in collaboration with external research assistants who will visit the facilities monthly (Table 1). Four research assistants will conduct in each facility observations of five ANC visits (first visit or between 24 and 28 weeks gestational age) to assess the information provided and the time spent on GDM. Furthermore, each woman who consented to participate in the study will be contacted post-partum by the local research assistants to conduct a structured survey on perceived quality of life/ care during her pregnancy and her expenses in relation to GDM.

**Table 1 Tab1:** Quantitative data and tools

Quantitative data collection	Tools
Health center performance	
No. of ANC consultations (total and new cases) No. of women tested for gestational diabetes (GDM) (at health center level/ at the external laboratory)	Structured monthly data collection form
No. of women tested with fasting blood sugar/ oral glucose tolerance test (OGTT) No. of women diagnosed with GDM No. of women with GDM referred out to see a specialist No. of women with GDM followed up for GDM at their health facility No. of women attending postnatal care (PNC) No. of women with a GDM attending PNC	
No. of women with a history of GDM in their last pregnancy re-tested during PNC Duration ANC consultation Time dedicated to GDM (information and testing) Information provided in relation to GDM	ANC observation checklist
Individual patient information	
Socio-demographic information; Obstetric history (medical/ past obstetric problems; gravida, para, LMP, height, weight); GDM specific information: testing (date/test/site), treatment (nutritional/medical), referral and follow-up visits (interval between visits; weight, blood sugar, treatment) Information about delivery (date/ place/ mode/ newborn weight/ APGAR/ newborn or maternal complications)	Structured individual patient data collection form
Information about diabetes re-testing post-partum (date/test used) Quality of life/care Expenses in relation to GDM	Patient survey

In each district two focus group discussions with up to two providers will be conducted separately for intervention and for control facilities to explore more in-depth their perceptions and experiences with GDM detection and management. Furthermore, we will conduct in-depth interviews with a subsample of 16 women participating in this study (see sample size) to get more insight how they experienced their pregnancy and the care received. In-depth interviews with key informants such as specialists at referral level as well as national and regional maternal and newborn health programme managers on their views of the intervention, its integration into the existing system and potential for scaling up will complement the picture.

### Data analysis

Quantitative data will be double entered into a pre-formatted excel file by the research assistants and converted into STATA Version 13 for further statistical analysis. The analysis will be applied on all recruited women following the intention-to-treat principle. Comparison of categorical variables will be done by using the chi-square/ Fisher’s exact test while continuous variables will be analyzed by using the Wilcoxon rank-sum test. Regression analysis will be applied to assess the relationship between the primary outcome birthweight and maternal determinants.

Qualitative data collection includes interviews with key informants, a sample of pregnant mothers and focus group discussions with providers. The recordings will be translated (those conducted in Arabic or Berber) and transcribed verbatim, followed by a thematic content analysis. Two independent researchers will code the data using NVIVO Version 11. Codes will then be grouped into categories and findings charted into a framework matrix.

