## Plain English summary

A situational analysis on gestational diabetes in Morocco revealed that pregnant women are experiencing difficulties in accessing GDM screening coupled with delays in receiving appropriate care for those affected. To evaluate a decentralized GDM detection and management approach through the primary health care level in Morocco, we are conducting a hybrid effectiveness-implementation research using a cluster randomized controlled trial design in two districts. In each district, 10 health centers were randomly selected with half of them serving as intervention and half as control facilities. In the intervention arm, women attending antenatal care will be screened for GDM and women positively tested will receive nutritional counselling and follow up through their health centers. In the control facilities, screening and initial management of GDM will apply standard practice. Birthweight of newborns of women with GDM will be compared between both groups and the prevalence of GDM at health center level assessed. We will further explore the quality of life and the care experienced by the women in both arms through a structured survey. In focus group discussions with providers we will explore and evaluate the feasibility of the intervention at primary level and its adoption by the health care professionals.

The findings of this study will be used to inform national stakeholders and are expected to contribute to an adaptation of the current strategy of detection and management of GDM in Morocco.

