## Background

In Morocco, a country with a total population of 33.8 million, an estimated 1.67 million people suffer from diabetes [1]. With a current prevalence of diabetes in Morocco of 7.7%, this number is expected to double in the next 20 years. [1] Women of childbearing age are not exempted from this development and alone in the MENA region, 3.7 million babies are born to mothers affected by gestational or pre-existing diabetes [1]. The prevalence of gestational diabetes (GDM) in Morocco is estimated to range between 8.2 and 10% [2, 3]. These figures originate from prevalence studies conducted at two university hospitals, but prevalence rates at lower levels of care are yet unknown. While Morocco has made considerable progress in lowering maternal mortality in the past decades [4], there is now an increased focus on maternal morbidity, including the effects of non-communicable diseases such as gestational diabetes on maternal and neonatal health [5].

Recommendations of high risk pregnancy management including the detection of GDM are available in Morocco and a fasting blood glucose test is routinely recommended to screen for diabetes during antenatal care (ANC). However, a situation analysis indicated that GDM screening is facing various obstacles particularly at the primary level of care. [6] These include gaps in provider knowledge, delays related to blood testing or to specialist referral. Oral glucose tolerance tests are not routinely prescribed unless on specific request. These delays in the detection and treatment of GDM impinge a timely management of affected women who as a result may end up with complications that could have been prevented. The detection and initial management of GDM during ANC through the first level of care could be an appropriate approach to establish timely interventions. However, it is uncertain if such a strategy would be feasible in the context of the Moroccan public health sector. To close this knowledge gap, the study presented in this protocol aims at implementing and evaluating GDM screening and follow up through first line health care services in Morocco.

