### Unit of randomization

The unit of randomization will be the health center (cluster). Cluster randomization rather than individual randomization will be applied to limit contamination between the different arms. In each of the two districts we will randomly select 10 health centers with at least 30 or more antenatal care consultations a month. Of these 10 health centers in each district, 5 are being randomized into the intervention group and 5 health centers serve as controls. As simple random selection does not account for contiguity, adjustments for “inter-cluster” effects will be done in the analysis stage.

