### Population and sample size

All pregnant women attending ANC will be eligible to participate in the study. Pregnant women with a known diabetes type 1 or 2 will be excluded from participation. In each health center, at least eight women diagnosed with gestational diabetes will be identified and followed up during their pregnancies and up to eight weeks post-partum. The sample size of minimum eight women per cluster was calculated based on the assumption that neonatal birth weight will differ in both groups with lower birthweights in the intervention arm due to earlier screening and treatment initiation at health center level. Based on comparisons of birthweight in treated versus untreated mothers [9, 10], for the assumption of a weight difference of 300 g between intervention and control group, a power of 80%, an alpha of 0.05 and an intra-class correlation coefficient of 0.1, we require 75 women with GDM in each arm.

A subsample of four women per district and arm will be selected for in-depth interviews based on the their educational level (≤primary / ≥secondary); and distance from the health center (<30 min / >1 h). Furthermore, the health care providers from both intervention and control facilities who are involved in GDM detection and management will be requested to participate in a focus group discussion (2 FGDs per district).

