### Intervention

In the intervention facilities, all women attending ANC will be offered a fasting glucose test at their first ANC visit and a 75 g oral glucose tolerance test (OGTT) if they are between 24 and 28 weeks pregnant. Tests will be done directly at the health center by capillary glucose testing using a standard plasma-calibrated glucometer. This corresponds to the latest consensus recommendations of FIGO for settings where no laboratories are available [11].

Women who are being diagnosed with gestational diabetes in the intervention facilities will receive nutritional counselling to start first a nutritional therapy combined with regular exercise for the duration of two weeks [12]. Standardization of nutritional counselling will be supported by an initial training of intervention site providers on nutritional education and accompanied by a nutritional guideline and a patient brochure for GDM in French and Arabic developed by the Moroccan Ministry of Health. In case dietary measures will not be sufficient to control glucose values within two weeks, women will be referred to an endocrinologist for further management. Follow-up will be assured through the health centers in close collaboration with the public endocrinologists. To standardize the procedure of screening, initial management and follow-up in the intervention facilities, study algorithms that are based on both nationally and internationally recommended glycaemia thresholds for GDM testing and monitoring have been developed in consultation with the national research group on GDM and regional endocrinologists at referral level (for algorithms see Figs. 1 and 2). The health care facilities that act as controls will screen for gestational diabetes and manage affected women according to their usual practice in accordance with existing national guidelines [13].

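### The birthweight comparison is confined to women diagnosed after randomisation by arm-dependent screening, so the intention-to-treat label overclaims and case mix can bias the result

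*Protocol article*

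**What the plan says.** Allocation is by health centre. Under Unit of randomization, of the ten centres in each district, "5 are being randomized into the intervention group and 5 health centers serve as controls". Under Population and sample size, the eligible population is broad: "All pregnant women attending ANC will be eligible to participate in the study", apart from women with known type 1 or 2 diabetes. The women followed are a subset: in each centre "at least eight women diagnosed with gestational diabetes will be identified and followed up". Data collection limits individual data to diagnosed women who consent, and the Plain English summary fixes the comparison: "Birthweight of newborns of women with GDM will be compared between both groups".

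The two arms find cases differently. Under Intervention, intervention centres offer all attendees an on-site capillary fasting test at the first visit, and a 75 g tolerance test to those at 24 to 28 weeks. Control centres "will screen for gestational diabetes and manage affected women according to their usual practice". The Background describes that practice: a fasting test is recommended routinely, there are delays and gaps in provider knowledge, and "Oral glucose tolerance tests are not routinely prescribed unless on specific request".

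Data analysis then says: "The analysis will be applied on all recruited women following the intention-to-treat principle". The adjustment stated for the primary outcome is for gestational age (Outcome variables). Data analysis adds a regression of birthweight on unspecified maternal determinants.

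**The concern.** Diagnosis happens after allocation, and the route to diagnosis is part of what is randomised. Membership of the analysis set is therefore a post-randomisation event that the arm can influence. Randomisation makes the centres' antenatal populations comparable in expectation. It does not do so for the women each arm's screening happens to find.

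If the two processes pick up women who differ in ways related to birthweight, the arms would differ with no treatment effect at all. Average glucose and complications would be affected in the same way. Women in control centres whose diabetes goes undetected drop out of the comparison altogether, so whatever the strategy gains by finding such women cannot show in the primary outcome. The results are meant to inform a decision on national scale-up, so a birthweight difference needs to be attributable to the strategy.

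**Working it through.** **1. The plan's own figure.** Population and sample size gives a 300 g difference, 80% power, alpha 0.05, ICC 0.1, at least 8 women per centre, and 75 women per arm. The article states no SD. Assuming SD 500 g and a two-sided test:
- n per arm before clustering = 2 × (500 × (1.960 + 0.842) / 300)² = 43.6, rounded up to 44
- design effect = 1 + (8 − 1) × 0.1 = 1.7
- 44 × 1.7 = 74.8, rounded up to 75

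This matches, so 500 g is a reasonable working SD, though still an assumption.

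**2. Precision of the comparison.** Ten centres per arm with eight women each give 80 per arm. SE = 500 × √(2 × 1.7 / 80) = 103 g. With 20 centres, a cluster-level t test has 18 degrees of freedom and a critical value of 2.101.

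**3. Illustration with no treatment effect.** Suppose a share f of intervention cases would be missed by usual practice, and their babies are on average d grams lighter than those of cases both methods find. The spurious difference is f × d. The chance of a significant result comes from the noncentral t with noncentrality (f × d) / 103.

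| f | d (g) | f × d (g) | Share of 300 g | P(significant, favours intervention) |
|---|---|---|---|---|
| 0.3 | 100 | 30 | 10% | 4.6% |
| 0.5 | 150 | 75 | 25% | 10.2% |
| 0.7 | 300 | 210 | 70% | 48.7% |

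The nominal value is 2.5%. For the 75 g row, an SD of 400 g gives 13.6% and an SD of 600 g gives 8.3%. If case mix differs by 75 g in the opposite direction, the figures swap: 10.2% for a significant result against the intervention and 0.4% for one in its favour. Neither f nor d is in the documents.

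**4. What produces the bias.** A simulation used the same layout (10 centres per arm, 8 women each, SD 500 g, ICC 0.1, no treatment effect, 1,000 runs per setting). Control detection either did or did not depend on severity, and severity either was or was not linked to birthweight.
- If either link was absent, the mean difference stayed within about 3 g of zero and two-sided rejection was 4.4% to 5.6%.
- If both were present, with birthweight rising 100 to 200 g per SD of severity, the mean difference was −44 to −139 g and rejection was 6.2% to 23.1%.

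Finding fewer cases in control centres is therefore not enough to bias the comparison. Detection must depend on something related to birthweight.

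**5. Whether the planned analysis removes it.** Adjusting for gestational age does not address who was diagnosed. The regression on maternal determinants is not tied to the arm comparison. The inter-cluster adjustment under Unit of randomization concerns contiguity of centres. The article does not mention differential case finding.

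**The case against.** Several stronger readings are tempting, and the documents do not support them.

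- **That the bias favours the intervention.** A reader might infer that the tolerance test adds milder cases with lighter babies, and that control cases are the severe ones. The article says neither. The obstacles listed in the Background are not said to depend on severity, and a fasting test is recommended in usual practice too. Leaving out undetected, untreated control cases could push the other way: if their babies are heavier, the control mean is too low. The net direction is open.
- **That the analysis is not intention-to-treat in any sense.** Analysing women by their centre's allocation meets the as-assigned part. What is missing is the randomised population.
- **That the error rates describe this trial.** They rest on assumed f, d and SD, and on a cluster-level t test, whereas the article names the Wilcoxon rank-sum test and regression. At the low end the effect is slight (30 g, about 5%).
- **That case definitions are known to differ.** The screening algorithm is a figure that is not shown, and the national guideline is only cited. A difference in thresholds is possible but cannot be read from the text.
- **That unblinded staff selected the women.** The article does not describe blinding. This is at most an inference from providers delivering the strategy.
- **That restricting the main comparison to fasting-positive women would cure the problem.** Fasting tests are also obtained differently by arm, so the selection would remain. If f were 0.3 to 0.7, reaching eight such women in an intervention centre would take 8/(1 − f), or about 11 to 27, diagnosed cases.

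Covariate detail may sit in a full protocol or analysis plan that is not shown. That does not answer the point, because the article itself fixes both the comparison population and the label. What stands against these objections is the structural fact that entry to the comparison depends on the arm.

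**Conclusion.** The point holds in a limited form. The primary comparison is conditioned on a diagnosis made after randomisation by an arm-dependent process. It is analysed as allocated but does not preserve the randomised comparison, so calling it intention-to-treat claims too much. Case mix can bias birthweight, average glucose and complications, and none of the stated adjustments removes that.

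Size and net direction are not determined by the documents. The 75 g example, with about 10% against 2.5% nominal, is illustrative and assumes an SD of 500 g, 80 women per arm, a design effect of 1.7 and no treatment effect. Over the range shown, the chance of a false result in the intervention's favour runs from about 5% to 49%. It falls below nominal if case mix differs in the other direction.

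**What to change.** In Data analysis:

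1. Remove the intention-to-treat label. Describe the analysis as a comparison of diagnosed women according to their centre's allocation.
2. Adjust the between-arm comparison, in addition to gestational age, for characteristics fixed before diagnosis and already on the patient form: height, parity, obstetric history and socio-demographic data.
3. Report by arm the numbers attending antenatal care, tested (by test type) and diagnosed. For diagnosed women, report test type, glucose value and gestational age at diagnosis. Table 1 already lists the counts and the test and its date. It lists blood sugar under follow-up but does not name the diagnostic value, so confirm that the form records it.
4. Pre-specify a sensitivity analysis restricted to women meeting the same fasting-glucose criterion in both arms. State that this reduces the selection but does not remove it.
5. Attribute a birthweight difference to the strategy only if these analyses agree.

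A supportive analysis of all eligible antenatal attendees may be added only where their birthweights are already available, since the plan collects individual data on diagnosed women only.

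Cost: changes of wording, somewhat more analysis, and a more cautious conclusion. The sensitivity analysis will also be smaller: with f between 0.3 and 0.7, 80 × (1 − f) leaves 56 to 24 of the 80 intervention women.

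### The named between-arm tests, in standard form, ignore the health-centre clustering that the randomisation and sample size assume: about 13% type I error at the protocol's own ICC if no between-centre variance lies between districts

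*Protocol article*

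**What the plan says.** **Randomisation.** Protocol article, Unit of randomization: "The unit of randomization will be the health center (cluster"). Within each of the two districts, of ten selected centres, "5 are being randomized into the intervention group and 5 health centers serve as controls". That makes 10 centres per arm, balanced by district.

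**Sample size.** Population and sample size: "The sample size of minimum eight women per cluster was calculated" "for the assumption of a weight difference of 300 g between intervention and control group", with "a power of 80%, an alpha of 0.05" and "an intra-class correlation coefficient of 0.1, we require 75 women with GDM in each arm". No SD for birthweight is given.

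**Primary outcome.** Outcome variables, Health effects, defines the birthweight comparison as adjusted for gestational age.

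**Analysis.** Data analysis names chi-square or Fisher tests for categorical variables and, for continuous ones, the "exact test while continuous variables will be analyzed by using the Wilcoxon rank-sum test". It adds a regression of birthweight on maternal determinants. It mentions no cluster term, random effect, robust variance or centre-level summary.

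**The one related statement.** Unit of randomization says that adjustment for inter-cluster effects will be made at the analysis stage. The reason given is: "As simple random selection does not account for contiguity". No method is named.

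**The concern.** Women attending the same health centre share staff, catchment and practice, so their outcomes are expected to be correlated. The sample size accepts this by using an ICC of 0.1. The tests named for the analysis do not: in their usual form they take each woman as an independent observation, which understates the variance of the between-arm difference.

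This is more than a detail that an article leaves to a fuller document. Specific tests are named, and they do not fit the stated design. An analysis plan that followed this text would produce p-values that are too small for birthweight, and for any secondary outcome with similar within-centre correlation. The trial is meant to inform a decision on national scaling up, so a false claim of effectiveness would have consequences.

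**Working it through.** **Inputs.** From the protocol: 10 centres per arm (5 in each district), at least m = 8 women per centre (80 per arm), ICC 0.1, difference 300 g, power 80%, alpha 0.05. Assumed: two-sided test, and an SD where one is needed.

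**1. The plan's own figure.** The required 75 per arm cannot be reproduced from the stated inputs alone, because the SD is missing. With an assumed SD of 500 g:

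- Unclustered n per arm = 2 × [500 × (1.960 + 0.842) / 300]² = 43.6, rounded up to 44.
- Design effect = 1 + (8 − 1) × 0.1 = 1.7.
- 44 × 1.7 = 74.8, so 75. This matches.

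An SD of 450 g gives about 60 and 550 g about 90. The stated 75 is therefore consistent with a design effect of 1.7 and an SD of about 500 g: the sample size allows for clustering.

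**2. Type I error of a test that ignores clustering.** The rate is approximately 2 × [1 − Φ(1.96 / √DE)] and does not depend on the SD.

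| ICC | m | Design effect | Type I error |
|---|---|---|---|
| 0.02 | 8 | 1.14 | 6.6% |
| 0.05 | 8 | 1.35 | 9.2% |
| 0.10 | 7.5 (75 per arm) | 1.65 | 12.7% |
| 0.10 | 8 | 1.70 | 13.3% |
| 0.10 | 10 | 1.90 | 15.5% |
| 0.15 | 8 | 2.05 | 17.1% |

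Simulating the Wilcoxon test itself (normal outcome, 10 × 8 per arm, ICC 0.1) gave 12.7% in 40,000 runs and 12.9% in a separate set of 20,000. A t-test on centre means held 5.0% to 5.1% in the same settings.

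**3. Effect of balancing by district.** Variance between districts is balanced across arms and cannot inflate the error. Set the total variance to 1 and let a share s of the between-centre variance (0.1) lie between districts. The factor by which the naive variance is too small is then 8 × [0.1 × (1 − s) + 0.9/8] = 0.8 × (1 − s) + 0.9.

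| Share s (assumed) | Factor | Type I error by formula |
|---|---|---|
| 0 | 1.7 | 13.3% |
| 25% | 1.5 | 11.0% |
| 50% | 1.3 | 8.6% |
| 75% | 1.1 | 6.2% |
| 100% | 0.9 | 3.9% |

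Simulated Wilcoxon rates agree: about 11%, 8% and 6% at 25%, 50% and 75%. A separate simulation that drew the district effects at random gave 8.9% at 50% and 4.5% at 100%.

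**4. What a replacement test must do.** An unstratified 10 v 10 t-test on centre means rejects only about 4%, 2.4% and 1.5% of true nulls at shares of 25%, 50% and 75%. It is conservative there and wastes power. Stratifying by district holds about 5% throughout.

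**5. Interval width, for illustration only (SD 500 g assumed).** Ignoring clustering, the half-width is 1.96 × 500 × √(2/80) = 155 g. Allowing for it, with 18 df, it is 2.101 × 500 × √(2 × 1.7/80) = 217 g. The ratio is 217/155 = 1.40.

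**The case against.** **The inter-cluster sentence may be meant as a clustering adjustment.** Its wording is loose, and a reader might conclude either that it settles the matter or that it is irrelevant. The text supports neither. Contiguity, the reason given, concerns neighbouring centres rather than women within one centre, but a broader intention cannot be excluded. What stands is that it names no method and the analysis section does not pick it up.

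**The regression may be the real primary analysis.** This has force. A standard rank-sum test cannot adjust for gestational age, which the primary outcome requires, and a regression could carry a random effect or a cluster-robust variance. As described, however, it relates birthweight to maternal determinants and names neither arm nor cluster. Nor would it cover the secondary outcomes.

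**The named tests can be adapted.** They can: there are clustered rank-sum and cluster-adjusted chi-square tests, and a rank-sum test can be run on the 20 centre means. The charge is only that the protocol names the tests without any such adaptation.

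**The 13% is conditional.** A reader might infer that the trial has 13% type I error whatever happens, or that every between-arm result is inflated. The documents do not support this. The ICC of 0.1 is a planning value given for birthweight only. One district is described as essentially urban and the other as rural and mountainous, so some between-centre variance may well lie between districts. If all of it did, there would be no inflation.

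**Conclusion.** The point holds. As written, the between-arm tests do not match the cluster randomisation or the ICC used to size the trial, and three sections (Unit of randomization, Population and sample size, Data analysis) are not reconciled.

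At the protocol's ICC and eight women per centre, a nominal 5% Wilcoxon test has about 13% type I error, provided that none of the between-centre variance lies between districts. It is about 9% at ICC 0.05, about 7% at ICC 0.02, and about 8% to 9% at ICC 0.1 if half of that variance is between districts. More than eight women per centre would raise it.

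These rates assume standard, unadapted tests and equal centre sizes. The simulations also assume a normal outcome. The conclusion that the text needs correcting does not depend on which of these rates applies. Because the error affects the primary comparison and the correction is cheap, it should be made before the data are analysed.

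**What to change.** - **Primary comparison.** State one of two analyses. (a) A cluster-level analysis of the 20 centre means of birthweight, adjusted for gestational age and stratified by district, on 16 df (20 centres less four district-by-arm cells) or 17 df (arm and district as main effects). (b) A linear mixed model or GEE with health centre as the cluster; arm, district and gestational age as covariates; and a small-sample correction. Choose one in advance, since they weight centres differently when centre sizes vary and eight is only a minimum.
- **Secondary between-arm comparisons.** Use the same approach, allowing for both centre and district. Keep the unadjusted chi-square, Fisher and rank-sum tests for description only.
- **Reconciliation.** Say in Data analysis what the inter-cluster adjustment is and whether it covers correlation within centres, contiguity between centres, or both. Say whether the birthweight regression includes arm.

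**Cost.** Only analysis wording changes; recruitment and data collection do not. Confidence intervals become wider, illustratively 217 g against 155 g half-width with an assumed SD of 500 g, before any gain from adjusting for district or gestational age. With the same SD, a cluster-level t-test on 18 df has about 77% power at 75 women per arm and 79% at 80, slightly below the 80% target.

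### Maternal height and parity are collected, but the article places neither in the arm comparison of birthweight: a precision gain forgone, not a shortfall against 80% power

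*Protocol article*

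**What the plan says.** Four places in the protocol article bear on this.

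- **Data collection, Table 1.** The individual patient form includes "Obstetric history (medical/ past obstetric problems; gravida, para, LMP, height, weight". The text above the table limits individual data to women diagnosed with gestational diabetes (GDM) who consented. No date is attached to the weight.
- **Data analysis.** The general rule is that "continuous variables will be analyzed by using the Wilcoxon rank-sum test". The next sentence is the only mention of a regression: "Regression analysis will be applied to assess the relationship between the primary outcome birthweight and maternal determinants". It does not list the determinants and does not say whether study arm is a term.
- **Outcome variables, Health effects.** The primary comparison is the birthweight difference between the groups, adjusted for gestational age.
- **Unit of randomization.** Inter-cluster effects are to be adjusted for at the analysis stage. Ten health centres per arm are randomized, five and five within each of two districts.

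Under Population and sample size, the calculation uses a 300 g difference, "a power of 80%, an alpha of 0.05 and an intra-class correlation coefficient of 0.1", and concludes "we require 75 women with GDM in each arm".

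**The concern.** The investigators treat maternal characteristics as relevant to birthweight, collect them on the women who will be analysed, and plan to model them. As written, that model serves to describe determinants, while the test named for continuous outcomes cannot use a covariate. An analysis plan that followed the Data analysis section literally would estimate the intervention effect without information already on the form.

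Two things are at stake. One is precision: predictors measured before treatment can remove part of the residual variance without recruiting anyone. The other is chance imbalance: with 10 centres per arm and about eight women per centre, differences in maternal size or parity between arms pass straight into an unadjusted birthweight difference. Randomizing within district balances the district contrast but not these characteristics within a district.

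**Working it through.** **Inputs from Population and sample size and Unit of randomization:** difference 300 g; alpha 0.05 (taken as two-sided, as sidedness is not stated); power 80%; ICC 0.1; 75 women per arm; 10 centres per arm; at least eight women per centre.

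**Not in the document, so assumed:** the SD of birthweight, and R-squared, the share of residual birthweight variance that the covariates explain beyond gestational age.

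**Step 1: the plan's own figure.** Required n per arm = 2 × (SD × 2.8016 / 300)² × [1 + (m − 1) × 0.1], where 2.8016 = 1.9600 + 0.8416.

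- With an assumed SD of 500 g, the first factor is 43.6, rounded up to 44. At m = 8 the design effect is 1.70, and 44 × 1.70 = 74.8, rounded up to 75. The stated figure is matched, but only with an SD near 500 g: at m = 8, 450 g gives 62 and 550 g gives 91.
- Nothing in the calculation takes credit for a covariate.

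**Step 2: implied SD at the planned size.** With 75 women in 10 centres, m = 7.5 and the design effect is 1 + 6.5 × 0.1 = 1.65. SD = 300 × √[(75 / 1.65) / (2 × 2.8016²)] = 510 g. At m = 8 it would be 503 g.

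**Step 3: standard error of the arm difference.** The variance of a centre mean, in units of SD², is 0.10 (between) + 0.90 / 7.5 = 0.12 (within). SE = √[2 × 510.5² × (0.10 + 0.12) / 10] = 107.1 g unadjusted. Two cases after adjustment:

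- both levels fall: (0.10 + 0.12) × (1 − R²)
- within centres only: 0.10 + 0.12 × (1 − R²)

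**Step 4: power.** Normal approximation: Φ(300 / SE − 1.96). Small-sample version: noncentral t on 2 × 10 − 2 = 18 df.

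| R² (assumed) | SE, both levels | Normal | t, 18 df | SE, within only | Normal | t, 18 df |
|---|---|---|---|---|---|---|
| 0 | 107.1 g | 80.0% | 75.5% | 107.1 g | 80.0% | 75.5% |
| 0.10 | 101.6 g | 84.0% | 79.7% | 104.1 g | 82.2% | 77.8% |
| 0.15 | 98.7 g | 86.0% | 81.9% | 102.6 g | 83.2% | 79.0% |
| 0.25 | 92.7 g | 89.9% | 86.4% | 99.5 g | 85.4% | 81.3% |

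A gain of five points on the normal scale needs an R² of about 13% if both levels fall, and about 23% if only within-centre variance falls.

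**The case against.** The strongest reply is that this rests on silence. The covariate list of a primary model is commonly left to an analysis plan, which is not shown, and the Data analysis section is one short paragraph. A reader might infer that the plan keeps arm out of the regression, or that the comparison is wholly unadjusted. The text supports neither. The regression sentence does not exclude arm, and the sections on outcomes and randomization promise gestational-age and cluster adjustment, so some adjusted comparison is intended.

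That reply stands as far as it goes. It does not remove the point, because the article names a test that cannot take any covariate and gives its one regression a different purpose. The predictors are in hand and using them costs almost nothing.

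Three further inferences should be resisted.

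- **That the trial is underpowered because of this.** The 75 per arm is matched with no covariate credit, so omission costs nothing against the stated 80%. The 75.5% in the first row comes from using a t reference for 20 centres, not from leaving covariates out.
- **That these data exist for all antenatal attenders.** They cover consenting women with GDM only. That is the birthweight analysis population, so the argument is unaffected.
- **That recorded weight is safely a baseline value.** Table 1 gives no date. If weight is first taken at or after diagnosis, its timing may depend on arm. The R² available may then be that of height and parity alone, which the documents do not give.

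The size of the gain is also open to challenge. R² is assumed, only variance beyond gestational age counts, and equal reduction at both levels is the favourable case.

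**Conclusion.** The point holds as a recommended improvement. The named test cannot use the maternal predictors, the only regression is described as a study of determinants, and no section places height, parity or weight in the arm comparison.

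For an assumed R² of 10% to 25% beyond gestational age, the forgone gain is about 4 to 10 percentage points of power if variance falls at both levels, or about 2 to 5 if it falls within centres only (normal approximation). On t with 18 df, power goes from 75.5% to about 80-86%, or about 78-81%. These figures rest on an unstated SD of about 510 g and would be smaller if height and parity explain less than 10%.

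The chance-imbalance argument is sound in principle, but the documents allow no figure for it. A reader might also expect adjustment to cure differences that arise because the two arms find cases differently: testing on site in one, usual practice in the other. It would not remove that bias.

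**What to change.** In Data analysis, make the primary analysis of birthweight one pre-specified regression that:

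- has study arm as the effect of interest and accounts for clustering by health centre;
- is reconciled with the gestational-age adjustment under Health effects and the inter-cluster adjustment under Unit of randomization;
- includes maternal height and parity as fixed baseline covariates, and maternal weight only if recorded before GDM diagnosis;
- reports the adjusted arm difference in grams with its 95% CI, the scale on which the sample size was set.

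State that the rank-sum test is not the primary test for birthweight. The determinants table can come from the same model.

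The cost is wording, two or three model terms, and a simple rule for missing covariate values, such as simple imputation of the baseline value. No new data or participants are needed.
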